### Participant recruitment

Participants will be recruited from the pool of patients receiving treatment in oncological facilities of the University Hospital Tübingen (UKT), and the Comprehensive Cancer Center Tübingen-Stuttgart including the psychosocial counselling facilities (Krebsberatungsstelle Tübingen) using flyers, posters, social media outlets and information provided by nurses, doctors, and psychologists. Patients in in- and outpatient oncological care at the UKT complete an electronic psycho-oncological screening (ePOS) as part of routine cancer patient care and are approached by the psycho-oncology services if indicated (see 39, 40). If they indicate symptoms of depression (rating of 3 or higher on PHQ-9), psychological distress (rating of 4 or higher on DT analogue scale) on the ePOS, their psycho-oncologist will ask if they are interested in participating in the study. Participants who indicate interpersonal distress (i.e. “no” for “Do you have someone to talk to about your worries”, “yes” for “familial problems”) will also be informed about the program and will be included in the pilot study if they meet the inclusion criteria. Information about the treatment program and ways of referral will also be sent out to practitioners who might treat cancer patients (general practitioners, oncologists, gynecologists, urologists, neurologists, surgeries, etc.) in the area around the clinic. Questions regarding the study will be answered via email, phone or in person. Those seeking participation will be screened for inclusion and exclusion criteria. Participants will not receive compensation for participating in the study. Recruitment will end when 40 patients have completed assessments. For the qualitative study, recruitment will end when saturation is reached as described below.

### Intervention

Group IPT addresses current findings on comorbid mental health conditions in cancer patients. It aims to enable patients to reduce symptoms of depression by reflecting and adapting the way they handle interpersonal role transitions and stressors. It is based on evidence-based methods of IPT and has been adapted to the challenges patients with cancer encounter by an expert panel for psycho-oncology care within the University of Tübingen. Previous research showed the efficacy of individual IPT for depressed patients with breast cancer, patients with HIV, and elderly patients, which share important characteristics with patients with cancer (23).

By addressing directly the difficult role changes patients with cancer face and by reflecting the role of acceptance and personal values in that transition, group IPT adapted for patients with cancer can empower patients to proactively engage with the novel situation and foster a sense of participation in the transition. By addressing how that role change affects patients interactions with their support system, group IPT adapted for patients with cancer can empower patients to (re-)gain access to social support. The group context provides patients with a group of reference with which to share experiences. Emotion-focused elements provide them with ways to communicate feelings and needs directly and effectively. In using patients’ personal conflicts and practicing different ways of engagement, group IPT adapted for cancer patients increases patients’ repertoire of interpersonal behaviors, enabling them to interact more flexibly within the changing and novel demands of their new roles. Thus, group IPT adapted for cancer patients can reduce depressive symptoms by addressing interpersonal stressors such as helplessness, loneliness, and lack of range in communication and interaction skills.

#### Intervention structure

The IPT intervention encompasses 10 weekly sessions of 60 minutes each. It is structured into modules incorporating IPT core themes: psychoeducation, role transitions (incorporating grief for the “lost healthy self”), and connection/interpersonal conflict. (**Table 2**) shows sessions, session content, therapeutic goals and patient homework for each module. Pre- and post-group treatment sessions will be held as described in (**Table 3**) (see 41). In pre-group treatment sessions, participants will set individual goals that fit within the IPT core themes and will be encouraged to work on them in group sessions by applying the session content to their specific examples (e.g. in role-play sessions). Post-group sessions will include a semi-structured interview encompassing questions on goal attainment, interpersonal experiences (42), outlook and change maintenance and questions regarding barriers and facilitators to participation and unintended effects of the intervention. Groups will consist of at least three and at most ten participants at a time and will remain in the same constellation across all ten group sessions.

**Table 2 T2:** Intervention modules description.

Session no.	IPT Problem Area	Content	Goals	Homework assignment
1	Psycho-education: cancer and mental health	• vulnerability-stress model • psychiatric comorbidities of cancer and “sick role” • resilience factors retained throughout cancer treatment • premises of IPT and application to struggles of patients with cancer	• Foster understanding of mental health issues in connection with cancer and treatment options • normalize distress/depression as a reaction to cancer diagnosis • empowerment • foster group coherence through shared experience of cancer diagnosis	• reflect strongest symptom of depression, apply coping/resilience as discussed
2	Role Transition: Introduction	• common role transitions for patients with cancer • transfer to individual role transitions • introduction to mindfulness exercises: 3-minute breathing space	• identify current changes and constants • reframe current changes as role transitions in wake of cancer diagnosis • normalize struggles adapting to change • foster group coherence by identifying shared struggles • foster reflection of individual, implicit connotations of new role	• reflect personal role transitions in wake of cancer diagnosis regarding three aspects: “what is lost?”, “what remains the same?”, “what is gained?”
3	Role Transition: emotion focus	• psycho-education: emotions • emotions commonly reported by cancer patients - fear/anxiety - shame - guilt - sadness - grief - hope	foster deliberate reflection of emotions • enhance emotional vocabulary and expression → prepare new interpersonal behaviors • reduce stigma of talking about uncomfortable emotions • encourage hope in spite of cancer diagnosis	deliberately observe emotional states and experiences throughout the week, take notes on coping strategies
4	Role Transition: Acceptance	• strategies for coping with challenging emotions commonly associated with cancer diagnosis/treatment • accepting uncomfortable emotions: living-with-your-monster metaphors	• educate about adaptive and maladaptive coping strategies • foster tolerance for uncomfortable emotions • support transition processes • foster serenity towards self and others	• try out new coping strategies, observe changes
5	Role Transition: Values	• psycho-education on values and mental health in context of personal health crisis • development of individual “compass of values” • develop individual behaviors to align new role with values	• foster reflection of and commitment to personal and interpersonal values • reframe current crisis as an opportunity for realignment with values and commitment to new values • create opportunities for post-traumatic growth from current crisis	• try one new value-based behavior
6	Role Transition: resources and isolation	• exploration and manifestation of personal resources (energy providers, energy takers) throughout cancer treatment • education on attention biases and connection to mood and fear of recurrence of cancer • introduction to gratitude exercises and self-compassion • lovingkindness meditation with application to cancer-specific struggles	• foster balanced view of lost and new roles • activate preexisting resources lost in cancer treatment • educate on possible new resources (gratitude journal, meditation) • foster sense of connection beyond oneself in current crisis	• implement one resource into everyday life • gratitude journal (continuously throughout the therapeutic process)
7	Connection	• education on communication • introduction to Kiesler Circle • transfer to individual and cancer specific interactions and difficulties • role-play and analysis: asking a doctor to repeat explanation of laboratory results	• foster self-efficacy in interaction • expand repertoire and flexibility of interpersonal behaviors esp. regarding medical context • strengthen dyadic coping	• use Kiesler Circle as framework for observation of interaction throughout the week
8	Connection	• Education on interpersonal relationship barriers and enablers • Practicing change of perspective • Transfer to Individual interactions: role-play and analysis with typical cancer-related situations	• expand repertoire and flexibility of interpersonal behaviors • apply theory to practice • strengthen dyadic coping	• try new behaviors • short analysis of a (conflict) interaction
9-10	Interpersonal Conflict	• education on conflict stages • practicing change of perspective • transfer to personal interactions: role-play and analysis with patients’ conflicts (iterating, chaining, shaping) • reflect changes in relationship connected to changes in interpersonal behavior	• foster deliberate, goal oriented reflection of conflict • expand repertoire of interpersonal behaviors • apply theory to practice • strengthen dyadic coping • strengthen/expand social network • evaluate and modify closeness circle	• try new behaviors • short situation-analysis of a cancer-related (conflict) interaction

**Table 3 T3:** Intervention schedule.

Modality	Goals	Duration
Individual Pre-Group	Determine patients’ personal treatment goals, explore focal areas, explore patients’ social network (closeness circle), inform about IPT group therapy rationale; study information and informed consent	60 min
Group (10 sessions)	See (**Table 2**)	60 min each
Individual Post-Group	Determine goal attainment, ensure maintenance of changes, feedback and remaining questions	60 min

The group will be led by a licensed psychologist-psychotherapist and a psychologist. They will both complete a three-day training course in IPT and will be supervised monthly by an external experience IPT supervisor ([name]).

#### Session structure

Every session begins with a short check-in (“How are you feeling coming in today? Are there things you would like to add regarding the previous session?”). After that, the previous session’s homework is discussed before opening the new session’s topic. Every session is concluded with a five-minute space for the participants to note down their personal take-home message(s), and a short check-in (“How are you feeling going home now?”, “Would you like to share a take-home message?”). After the short introduction to mindfulness practices in session two, all sessions are concluded with a joint mindfulness exercise (Three-minute breathing space).

To reflect adequately the context of outpatient psycho-oncology treatment, the intervention is deliberately aimed at patients currently undergoing oncological treatment as well as survivors who have completed acute treatment. With trajectories and side effects of cancer treatments being rather unpredictable in some cases, patients are expected to miss sessions every now and then. A one-on-one session via telephone, or in case of in-house treatment in person, will be offered to patients to catch up on the content of the missed session. Treatment will be considered completed if patients have attended or caught up with at least eight of the ten sessions in total and have not missed more than four group sessions in total. Pre- and post-intervention sessions are mandatory. Attendance and catch-up-sessions will be registered.

### Outcome measures

#### Feasibility outcomes

Feasibility measures will include recruitment rates and adherence to treatment, suitability of criteria for exclusion and inclusion, suitability of data collection procedures, and suitability of recruitment procedures. Participant flow will be documented according to CONSORT guidelines (38). Challenges in trial organization and changes to amend difficulties will be documented in the study teams meeting protocols. Therapists’ adherence to the intervention manual will be documented using supervision session protocols and the IPT scale of Strategies in Therapy Use Form – Therapist Version (STUF) developed by Swartz et al. (43). Documentation of reasons for drop-out and documentation of the post-intervention session will provide information on previously disregarded patient reported outcomes, suitability of study procedures according to the participants, and unintended effects of the intervention.

Participant adherence to treatment will be used as primary criterion for trial progression, with an adherence rate above 80% indicating progression (‘Green/Go’), an adherence rate between 80% and 40% indicating progression only after thorough revision and amendment (‘Amber/amend’) and an adherence rate below 40% indicating no progression (‘Red/stop’) (44). Status regarding the progression of the trial will be assessed regularly in the study teams meetings and documented in meeting protocols, along with changes to the protocol that might be implemented to amend adherence rates. Qualitative data will be used to inform amendments to study procedure and intervention structure or content.

#### Preliminary efficacy outcomes

Assessment will contain German versions of the following instruments:

- Sociodemographic and medical data (self-generated items)- Patient Health Questionnaire (PHQ-9) (45–47) (9 items reflecting the diagnostic criteria of DSM-IV depressive disorders)- General Anxiety Disorder Questionnaire (GAD-7) (48, 49) (7 items reflecting the most prominent diagnostic criteria of DSM-IV generalized anxiety disorder)- Distress Thermometer analogue scale and problem areas (DT) (50, 51) (screening tool assessing overall distress in cancer patients on a scale of 0 to 10 and listing possible physical and psychosocial problem areas)- Revised UCLA Loneliness Scale (R-UCLA) (52, 53) (20 items assessing loneliness)- Brief Social Support Scale (BS6) (54) (6 items assessing perceived emotional and tangible social support)- Interpersonal Needs Questionnaire (INQ) (55, 56) (15 items assessing the interpersonal concepts of thwarted belongingness and perceived burdensomeness)- Interpersonal stressors (4 self-generated open-ended questions assessing burdensome relationships, distressing role changes, conflicts)- Quality of Life (EQ-5D-3L) (57, 58) (5 Items assessing general quality of life in a descriptive system regarding mobility, self-care, usual activities, pain/discomfort and anxiety/depression)- Hornheider Screening Instrument (HSI) (59) (7 items assessing need for psychosocial care in patients with cancer)

Qualitative data will be used to inform on previously disregarded outcomes and the lived experience of the participants.

The schedule of the assessments is summarized in (**Table 1**). Data will be collected through an online survey designed using RedCap electronic data capture tools hosted at Tübingen University (36, 37). Participants will receive a link to the survey via email. The assessment will take about 30 minutes to complete. It can be paused and accessed again at a later point in time using a personal code. Each measure constitutes one page in the survey. Survey answers cannot be changed once the page has been submitted, and a new page cannot be opened until all items have been answered. Participants will be assigned a random number generated using MATLAB 2023a (60) Random Number Generator with current time as seed (rng(‘shuffle’); rand). All data in the assessment will be recorded under that pseudonym only.

Primary outcome will be symptoms of depression at completion of the treatment and 3-months follow-up, which will be assessed using the Patient Health Questionnaire (PHQ-9). As secondary outcomes we chose symptoms of anxiety, which will be assessed using the Generalized Anxiety Disorder Questionnaire (GAD-7), and psychological distress as measured by the Distress Thermometer (DT) at completion of the treatment and 3-months follow-up. Tertiary measures are self-reports of loneliness as measured by the R-ULCA Loneliness Scale, perceived social support as measured by the Brief Social Support Scale (BS6), interpersonal needs (perceived burdensomeness and thwarted belongingness) as measured by the Interpersonal Needs Questionnaire (INQ) at completion of the treatment and 3-months follow-up.

Qualitative data will consist of the audio recording of the post-intervention semi-structured interviews. Records will be saved using the patient pseudonym on study tablets that are not connected to the internet and will be transcribed by the study team. Recordings will be deleted after analysis is completed. A translation of the interview guidelines can be seen in (**Table 4**).

**Table 4 T4:** Post-intervention semi-structured interview.

Topic	Question
Goal achievement and relevance to everyday life	In the preparatory session, you formulated the following goal for the group therapy: X What has changed in relation to X since the start of therapy? How do you notice the change in everyday life? What would you say - have you achieved, partially achieved or not achieved the goal? Which aspects of the group therapy did you find helpful regarding X? Which aspects did you find inappropriate or not useful? Have there been any changes in your everyday life beyond the goals we just talked about? How do you observe these changes? How is the change related to the group therapy? What interpersonal experiences do you take away from the group?
Challenges and adverse effects	What were the particular challenges or difficulties for you in group therapy? How did the therapists or the group support you in overcoming the challenges? (How could the therapists or the group have supported you better in overcoming the challenges?) Did group participation have adverse effects for you?
Organizational barriers and facilitators	How did you feel about the organizational aspects of group therapy? What were barriers to participation? What facilitated participation? How did you feel about the organizational aspects of the study (consent, information flow, questionnaires, interviews)? What were barriers to participation? What facilitated participation?
Outlook	Looking at the time after the group therapy: What are your goals, what changes do you want to make? How can the therapists or the group support you with that? What are you worried about? How can the therapists or the group support you with that?
Other	Is there anything else you would like to share with us?

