### Sample size calculation and statistical analyses

All quantitative data analyses will be conducted using R (61), RStudio (62), and MATLAB (60).

Due to the nested nature of group intervention data (63) and more specifically the scarcity of research regarding IPT in patients with cancer other than breast cancer, sample size calculations are to be treated with caution. A sample size of 40 participants is considered appropriate for this feasibility study.

Feasibility outcomes will be analyzed using percentages. Descriptive analyses of sociodemographic data will be conducted. Preliminary efficacy will be analyzed in within-subject comparisons for each outcome measure and reported with 95% confidence intervals (CI). Results regarding the primary outcome (symptoms of depression, PHQ-9) will be considered indicative of efficacy if the CI is above zero and includes the predefined Minimal Clinically Important Difference (MCID) of 5 points as previously determined by Löwe et al. (64). Results regarding secondary and tertiary outcomes will be considered indicative of efficacy if it is above zero.

Missing data will be reported as such. It is expected that at least a subset of dropouts may nevertheless be available to complete the post-treatment assessment, improving the accuracy of data collected. An interim analysis is not planned.

Qualitative analysis will be conducted using MAXQDA 2022 software (65). Record transcripts will undergo qualitative content analysis as described by Mayring (66) using deductive-inductive category formation, starting with an initial batch of 6 interviews. Iterative analysis will continue until saturation is reached. Procedures and results will be recorded and reported in accordance with the Standards for Reporting Qualitative Research (SRQR) (67). Saturation will be assessed using the 16-item checklist provided by Ahmed (68). Saturation will be defined as lack of emergence of new themes in three consecutive interview transcripts. Meta-analysis indicates a sample size of 13 is enough to reach saturation for most studies (69). Analysis will focus on the following aspects included in the semi-structured interview (**Table 4**): changes in everyday life, helpful elements of group IPT, inappropriate elements of group IPT, interpersonal experiences in group IPT, challenges in group IPT, support regarding challenges, adverse effects, barriers and facilitators for participation in group IPT and study procedures, and outlook.

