### Ethics and dissemination

The pilot study has been reviewed and approved by the ethics committee of the faculty of medicine of Eberhard-Karls-University of Tübingen (Reference No 177/2023BO2). The qualitative aspects of the study (audio recording of post-intervention interviews, qualitative content analysis of recordings) were the subject of an amendment to the original review and have not yet been approved. Qualitative data collection and analysis will not commence until approval is received. Results will be published in peer-reviewed journals and conference presentations.

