## Discussion

In this pilot study in 40 patients, we propose to develop and evaluate an IPT group treatment for symptoms of depression specifically tailored to the needs of patients with cancer and comorbid symptoms of depression.

The described study is a pilot study, and information gathered will be limited by the exclusive use of self-report data and the naturalistic design without any control group. A lack of resources, potential difficulties in recruiting participants and ethical considerations led to the decision not to apply a randomized controlled design.

The naturalistic group composition of patients with diverse types of cancer and in different treatment stages increases the generalizability of findings from this study. It also adds to its value for care providers within the psycho-oncological services who also treat patients from all specialties and at all points in the patient journey. Participants may even profit from the different perspectives and experiences shared in more heterogenous groups.

Our preliminary findings will suggest whether a trial of group IPT is feasible and indicate preliminary efficacy in reducing symptoms of depression in patients with cancer. We will also assess changes in symptoms of depression, anxiety, and in interpersonal factors such as loneliness, thwarted sense of belonging, perceived burdensomeness, and perceived social support. The findings will inform us how to adapt and change the program in order to make it more efficient or feasible for patients and care providers. Qualitative content analysis will enrich our understanding of the lived experience of participants regarding feasibility and acceptability of intervention and study procedures and provide qualitative insight into everyday changes for patients.

Adequate and efficient treatment for depressive symptoms in patients with cancer is urgently needed. The proposed group IPT program adapted for cancer is a novel, unique and promising approach to the problem. An effective treatment for symptoms of depression in patients with cancer is highly relevant because depressive symptoms affect a large proportion of patients with cancer, and have detrimental effects on patients’ quality of life, treatment compliance, and even mortality (5).

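### The interview guide's only question on the source of a change takes a link to the group therapy as given, and no question invites another cause

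*Protocol article*

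**What the plan says.** Table 4, under Preliminary efficacy outcomes in the protocol article, is presented as the interview guide in translation, with no sign that it is an excerpt. Its first block deals with change in two strands.

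- **Goal-related change.** The interviewer asks "What has changed in relation to X since the start of therapy", where X is the patient's own goal. Questions follow on how the change shows in daily life and how far the goal was reached, and then "Which aspects of the group therapy did you find helpful regarding X". A matching question covers aspects that were unsuitable or of no use.
- **Other change.** The interviewer asks "Have there been any changes in your everyday life beyond the goals we just talked about", then how the patient observes these changes, and then "How is the change related to the group therapy".

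The article gives the interviews three uses. Under Feasibility outcomes they inform amendments to study procedure and to the structure or content of the intervention. Under Preliminary efficacy outcomes they inform on overlooked outcomes and patients' lived experience. The Discussion adds insight into everyday changes. It also lists among the study's limitations "the naturalistic design without any control group".

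**The concern.** A question that asks how a change relates to the therapy assumes that it does. A patient whose everyday life improved because a course of cancer treatment ended, or because other help arrived, can say so only by going against the question or by raising it unasked.

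This matters more here than in a controlled study. With no comparison group, the interviews are the only described place where patients could say what they think brought about their change. Other causes are also built into the population. The Session structure section says the intervention is aimed at patients in current oncological treatment as well as survivors. Participant eligibility admits patients on antidepressants, who are to report changes in medication. It also selects on raised PHQ-2 and Distress Thermometer scores, so some improvement with time alone is plausible.

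At stake is the quality of the qualitative material. If elements of the group are credited with changes that came from elsewhere, the team may keep or expand them for the wrong reason when it revises the programme.

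**Working it through.** No formula applies, so the check is a reading of every question in Table 4 against the planned uses of the interviews.

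**Count of questions by block:** goals and everyday life 9; challenges and adverse effects 4; organizational aspects 6; outlook 4; other 1. Total 9 + 4 + 6 + 4 + 1 = 24.

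**Questions that tie a change or effect to a source:**

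| Question (paraphrased unless quoted) | Source named | Room for another cause |
|---|---|---|
| "Which aspects of the group therapy did you find helpful regarding X" | Group therapy | Not asked |
| Unsuitable or useless aspects | Group therapy | Allows criticism, not another cause |
| "How is the change related to the group therapy" | Group therapy, link assumed | Not asked |
| Adverse effects of taking part | Group participation | Allows harm, attributed to the group |

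All four name only the group. Only the third asks for the source of a reported change, and it follows the strand on changes beyond the goals. In the goal strand no cause is asked for at all; the helpful-aspects question simply offers the group as the contributor. The number of questions that invite a cause outside the group is 0 of 24. That figure is a plain count and not a measure of bias, since most of the 24 questions (organization, outlook, challenges) are not about causes.

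**Does the analysis make up for it?** The analysis section lists the aspects on which coding will focus, beginning with "changes in everyday life, helpful elements of group IPT, inappropriate elements of group IPT, interpersonal experiences in group IPT". Coding is deductive-inductive, so a category for outside causes can emerge, but only from what patients volunteer. Saturation is defined as no new theme in three consecutive transcripts. It can therefore be reached without outside causes having been explored.

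**Does anything quantitative rest on it?** Progression is decided on adherence, with cut-offs at 80% and 40%. Efficacy is read from the PHQ-9 confidence interval and from the intervals of the other scales. Neither uses the interviews. The Objectives section says all collected data will inform the decision on a full trial, but it attaches no rule to the interviews.

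**The case against.** The case on the other side has several parts.

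- **Format.** The interview is semi-structured and the printed text is a translation. A patient can answer that there is no relation, the opening questions on change are neutral, and there is a closing open question. This stands as a limit on the strength of the effect. It does not supply a planned prompt for other causes.
- **Other records.** Medication changes are reported, shortened medical data are collected again after treatment, and the Distress Thermometer lists problem areas. These show that competing events happened, not what patients think caused their change.
- **Admitted limits.** The Discussion concedes self-report and the lack of a control group. It does not concede that the guide presumes attribution.

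Three stronger readings are tempting, and the document does not support them.

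1. A reader might infer that the interviews falsely corroborate the PHQ-9 result. No section uses them to test or support that result.
2. A reader might infer that every interview reporting a change is pulled towards the group. The question follows only changes beyond the stated goals, and it could equally draw a worsening towards the group.
3. A reader might count the list of analysed aspects, or the question "How did the therapists or the group support you in overcoming the challenges", as further errors. The list is a focus for coding and not a closed codebook, and its aspect on everyday changes is not tied to the group. The support question concerns difficulties within the group, not the cause of change.

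**Conclusion.** The point holds in a limited form. The guide's single question on the source of a change presumes the group, the goal strand offers only the group as contributor, and no question invites another cause. In an uncontrolled study with patients who may be in active cancer treatment, this can lean patients' accounts of everyday change, and the amendments to content that they inform, towards the group.

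The size of the lean cannot be derived from the document. No decision rule and no PHQ-9 conclusion depends on it. The conclusion assumes that the printed translation reflects the wording used and that interviewers follow it without a neutral probe of their own. It also assumes that the self-generated acceptability items given after treatment, which are not shown, do not already ask about other causes. It is a modest improvement to make, worthwhile because it is cheap and still possible.

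**What to change.** In Table 4, for both goal-related and other changes, ask in this order:

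1. *What do you think led to this change?*
2. A prompt for influences outside the group: cancer treatment or its course, medication, other support, other events.
3. *What part, if any, did the group play?*

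The third question replaces the present one on the relation to the group. Code the causes named (group / other / unsure) under the existing aspect on everyday changes.

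The cost is one or two extra minutes per interview and one more code. The timing is favourable: the Ethics section says the interview recording and its analysis "were the subject of an amendment to the original review and have not yet been approved", and that qualitative collection will not begin until they are. The revised guide can therefore be used from the first interview, though it should go to the ethics committee with the pending amendment.
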